**Methods:**

The longitudinal quasi-experimental study will be undertaken in two purposively selected blocks of one district each in the four intervention states and one comparison state. From each state, 200 SAM children identified using weight-for-length/height z-score (WHZ) < **−** 3 criteria will be enrolled in the study. Their anthropometric data and skinfold thickness will be taken on admission, at sixth week and at discharge by trained field investigators. Other child details, incidence of morbidity and socio-economic details will be collected on admission. To assess food consumption pattern including consumption of locally produced nutrient dense food supplements, dietary assessment, using 24-**h** dietary recall will be conducted on admission, at sixth week and at discharge. In addition, body composition parameters will be assessed for a sub-set of children using bio-electrical impedance analysis on admission and at discharge to analyse changes in total body water, fat-free mass, and fat mass. Post discharge, all study participants will be followed up monthly until 6 months. Atleast 10% of the sample will be checked for quality assessment.

The study’s primary outcome is cure rate defined as children attaining WHZ **≥** -2. Secondary outcomes include mean weight gain, mean length of stay, body composition parameters, relapse and mortality rates. Additionally, process evaluation and cost effectiveness analysis will be conducted.

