### Intervention strategy

In general, the State Governments of Telangana, Madhya Pradesh, Odisha and Chhattisgarh will implement community-based management of SAM (CSAM) programme adapted from the WHO guidelines, in addition to the existing government nutrition promotion interventions. The approach will incorporate active and/or passive case-finding and screening for severe wasting by government frontline nutrition and health workers. For uniformity, children with WHZ < -3 will be categorized as experiencing SAM. SAM children will further undergo medical examinations and appetite test to identify complicated and uncomplicated cases. All complicated cases will be referred to the nearest nutritional rehabilitation centres (NRCs) for in-patient management. All uncomplicated cases will be enrolled in the CSAM programme for their community-based management in *anganwadi centres*. While the program’s primary focus is on treatment of children who are severely wasted, key activities also include regular follow up of all enrolled children at the *anganwadi centers*, counseling of caregivers on infant and young child feeding (IYCF), safe water, sanitation and hygiene practices, family planning and child care practices, promotion of vaccinations, appropriate referrals of sick children to NRCs or public health facilities and post discharge follow up. SAM children enrolled in the programme will also be given locally produced nutrient dense food supplements, antibiotics, anthelminthic and micronutrient supplements. Key aspects of the state specific CSAM programme are presented in Table 1. Detailed description of the state specific CSAM protocols and nutritional content of each locally produced nutrient dense food supplement is provided in Additional file 1. In the comparison area, where no CSAM intervention is being implemented, SAM children identified and enrolled in the study will receive the existing government nutrition promotion interventions. The existing program includes provision of double quantity of Take Home Ration (THR)^1^ for severely underweight children (which covers most of SAM children) and identification and referral of SAM children to Malnutrition Treatment Centres (MTCs).

**Table 1 Tab1:** Key aspects of the CSAM protocol that vary per state assessed

States	Screening & Identification	Admission criteria	Maximum treatment duration	Discharge criteria	Nutrient dense food	Post-discharge Follow up

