#### Secondary research questions

Do state specific CSAM programmes help recovery of a SAM child, as defined by body composition parameters such as fat mass by skinfold thickness and fat free mass, body water by BIA, in each of the four intervention states?What is the relationship between anthropometry and body composition measures in a child suffering from SAM, in each of the five states?Do state specific CSAM programme provide better outcomes in terms of recovery, defaulting, death, length of stay and average weekly weight gain, compared to existing evidence from India?Which of the CSAM programme provides best rate of recovery 6 months after exit from the programme, defined by the relapse and mortality rates?

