### Selection of study samples

In each of the CSAM intervention states, 200 SAM children aged 6–59 months identified using WHZ < -3, who will be enrolled in the CSAM programme and who do not have any medical complication and pass the appetite test will be enrolled in the study. Similarly, in the comparison state, 200 SAM children aged 6–59 months will be identified using WHZ < -3 by the Field Investigators and enrolled in the study, who do not have any medical complication and pass the appetite test. Children identified between October’ 2020 and December’ 2020 will be enrolled in the study.

We will exclude SAM children with presence of emergency signs, edema, high fever, cough with fast breathing and known secondary SAM cases like neurological diseases such as cerebral palsy, TB, HIV congenital heart defects, congenital structural defects and cleft palate. However, if any child enrolled in the study develops any medical complication later during the course of the study, s/he will be referred to inpatient care but continued to be part of the study.

The sub-set of children (first 50% of the enrolled children i.e. 100 children in each state) with weight at enrollment > 5 kg will be selected for body composition, as the BIA machine can only give accurate measurement for children with weight > 5 kg. So in total, 500 children will be selected for studying their body composition in the five study states.

For identifying eligible study participants in the CSAM intervention states, SAM children to be identified and enrolled by the frontline workers according to the identification criteria of the state specific CSAM programme from each of these selected *anganwadi centres*, will be rechecked by field investigators within 72 h and those children who will qualify on the basis of inclusion and exclusion criteria of the study, will be enrolled in the study. Similarly, in the comparison state, Field Investigators will identify eligible study participants and enroll in the study. Field Investigators will then approach caregivers of the children to explain the study and seek their written consent for participation. They will also be asked for permission to follow-up their children during the treatment phase and for 6 months’ post discharge in order to measure the impact of the interventions.

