### Data analysis

Final analysis will include all children enrolled in the study. Appropriate quantitative analyses will be used including descriptive statistics (proportion, percentage, mean or median), comparison of difference in proportion for binary outcome using Pearson chi-square and comparison of average change for continuous variable using t-tests. Recovery will be compared for effectiveness of state specific CSAM protocols and locally produced nutrient dense food supplements in four intervention states in comparison to the comparison state. Cox regression method will also be used for this analysis by defining recovery as event, as it can utilize the entire sample size including defaulters or loss to follow up. Other parameters including skinfold, defaulting, death, length of stay, average weekly weight gain and height gain will also be compared between the intervention states and the control state. Subgroup analysis will be done for comparing recovery among children aged 6–23 months and 24–59 months between intervention states and control state. For the sub-sample of body composition, change in fat mass, fat free mass and body water will be compared between the four intervention states and the comparison state. A linear mixed model will be developed for different outcomes (recovery, weight gain, and body composition parameters) adjusting for various random and fixed effects across all sites adjusted for differences at baseline.

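### Defaulting and length of stay are to be compared with a control state that has no CSAM admission, discharge or default rule, so differences in exit rules can pass for programme effects

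*Protocol article*

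**What the plan says.** The Data analysis section lists the outcomes to be set against the control state beyond recovery: "defaulting, death, length of stay, average weekly weight gain and height gain will also be compared between the intervention states and the control state". The abstract makes length of stay a named secondary outcome: "Secondary outcomes include mean weight gain, mean length of stay, body composition parameters, relapse and mortality rates".

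The Intervention strategy section describes care in the control state, introducing it with "In the comparison area, where no CSAM intervention is being implemented". Study children there get the government's usual nutrition services. Those services are described as follows: "The existing program includes provision of double quantity of Take Home Ration" for severely underweight children, together with "identification and referral of SAM children to Malnutrition Treatment Centres (MTCs"). Under Selection of study samples, children in the intervention states are already enrolled in the CSAM programme when they are rechecked for the study. By contrast, "in the comparison state, Field Investigators will identify eligible study participants and enroll in the study".

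Table 1 gives admission criteria, maximum treatment duration and discharge criteria for Telangana, Madhya Pradesh, Chhattisgarh and Odisha. It has no row for Jharkhand.

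The third secondary research question asks about the CSAM programmes' "recovery, defaulting, death, length of stay and average weekly weight gain, compared to existing evidence from India".

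**The concern.** Length of stay and default describe a child's passage through a treatment programme: admission, attendance, and discharge or failure to return. The CSAM states have such a programme with stated rules. The control children enter the study, and no CSAM rule governs when they leave. A comparison of the two groups therefore sets a programme quantity against something else, and the article does not say what.

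The result could be misread in either direction. If the value entered for control children reflects the study timetable, CSAM stay can look shorter although recovery is the same. If control default is zero because there is nothing to default from, CSAM looks worse although no more children were lost to the study. The Discussion says strategies can be scaled up if they improve the primary and/or secondary outcomes, so an artefact in a named secondary outcome could enter that argument.

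**Working it through.** **Plan's own figures.** The article gives no expected length of stay or default rate, so there is none to reproduce. The group size used below is the stated 200 per state, from 100 per age group. That figure is reproduced: (1.960 + 0.842)² × (0.50×0.50 + 0.25×0.75) / 0.25² = 7.849 × 7 = 54.9, rounded to 55; × 1.5 = 82.5; × 1.2 = 99, close to 100. Nothing below depends on how it was derived.

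**Inputs from the article.**
- Maximum duration is 12 weeks in one CSAM state and 16 in the other three (Table 1; Sample size).
- No end point is stated for the control state.
- Study measurements before post-discharge follow-up are at admission, week 6 and discharge (Data collection; Table 2).
- Expected cure rates are 25% and 50% (Sample size), used here as a range for a common rate.
- Binary outcomes are compared by Pearson chi-square (Data analysis).

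**Assumptions not in the article.** Recovery time T is exponential with the same hazard in every state, so there is no true effect. CSAM workers check weekly and discharge at the first check after recovery. There is no clustering.

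**Length of stay.** For a 16-week cure rate c, the weekly probability of remaining unrecovered is q = (1 − c)^(1/16): 0.98218 for c = 25% and 0.95760 for c = 50%.

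- Weekly checks with cap K: mean stay = (1 − q^K)/(1 − q).
  - K = 16: 0.25/0.01782 = 14.03 weeks; 0.50/0.04240 = 11.79 weeks.
  - K = 12: 0.1941/0.01782 = 10.89 weeks; 0.4054/0.04240 = 9.56 weeks.
- Exit seen only at week 6 or 16: mean stay = 6 + 10 × q⁶ = 6 + 10 × 0.8977 = 14.98 weeks; 6 + 10 × 0.7711 = 13.71 weeks.
- Every child assigned 16 weeks: 16.00.

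| CSAM rule | Control rule | Apparent reduction, c = 25% | c = 50% | z at 200 per state |
|---|---|---|---|---|
| Weekly, cap 16 | All assigned 16 | 1.97 | 4.21 | 6.8; 11.2 |
| Weekly, cap 16 | Week 6 or 16 only | 0.95 | 1.92 | 2.6; 4.0 |
| Weekly, cap 12 | Weekly, cap 16 | 3.14 | 2.23 | 9.0; 4.9 |
| Weekly, cap 16 | Weekly, cap 16 | 0.00 | 0.00 | 0 |

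The third row also runs in reverse. If the control window were 12 weeks, a 16-week CSAM state would look longer by the same 2.2 to 3.1 weeks. Because the CSAM maxima differ among themselves, no single control cap matches all four states.

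**Default.** With x of 200 in a CSAM state and 0 of 200 in the control by definition, chi-square = 400 × (200x)² / (200 × 200 × x × (400 − x)) = 400x/(400 − x).
- x = 4 (2%): 1600/396 = 4.04, above 3.84, so p < 0.05 on the test the plan names. Expected counts are only 2 per cell here. An exact test gives 2 × (200·199·198·197)/(400·399·398·397) = 0.12.
- x = 10 (5%): 4000/390 = 10.3.
- x = 20 (10%): 8000/380 = 21.1.

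At 5% or more the difference is clear on any test, and it counts against CSAM.

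**The case against.** The strongest reply is that the article supports a study-level reading. Table 2 covers all enrolled children and has an exit or discharge column, and the abstract gives all participants a post-discharge phase. The Data analysis section runs a Cox model of recovery that retains defaulters and losses to follow-up. On that reading, stay is enrolment to exit and default is non-completion, and both can be computed for control children. The full protocol may define both terms, and an article may leave definitions to it.

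Much of this stands, and it rules out several stronger readings that a reader might infer.

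- That an effect must appear by construction. It need not: one exit rule, one cap and one visit schedule give a difference of zero. The 2.0 to 4.2 weeks requires control children to be assigned 16 weeks, which the article nowhere says.
- That control children receive no programme at all. Existing services and referral continue; what is absent is CSAM.
- That nothing is measured in the control state from which an interval could be formed. Table 2 provides an exit measurement.
- That the third secondary research question contradicts the Data analysis section. It names another comparator for these outcomes, and for recovery, death and weight gain as well. The analysis section adds the control state.
- That the artefact always favours CSAM. For default fixed at zero in the control, it runs the other way.

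The reply does not remove the point. A study-level reading is free of bias only if exit rule, window and frequency of checking agree across states. The article's own maximum durations already differ, so a definition of terms alone would not make length of stay comparable. The comparison is also one the article commits to, so the point is more than a missing definition.

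**Conclusion.** The point holds in conditional form. In their programme meaning, default and length of stay have no counterpart in the control state. In a study-level meaning, length of stay reflects exit rules that differ between states.

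With no true effect, the apparent difference in stay is 2.0 to 4.2 weeks, about 1 to 1.9 weeks, or 2.2 to 3.1 weeks, depending on which difference in rules applies. It is zero when rules and cap agree. These sizes rest on exponential recovery, a common 16-week cure rate of 25% to 50%, weekly programme checks and no allowance for clustering. Other checking intervals would change them. The default artefact arises only if control default is zero by definition; if default means loss to study follow-up in every state, none is built in.

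This should be corrected, because a named secondary outcome is affected. It does not touch the cure-rate comparison itself.

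**What to change.** In the Data analysis section, take programme default and length of stay off the list compared with the control state. Report them for the four CSAM states only, described against existing Indian evidence as the third secondary research question asks, and note that stay is capped by each state's maximum duration.

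For the comparison with the control state, use two quantities defined identically in all five states:
- study loss to follow-up, under that name;
- time from enrolment to WHZ ≥ −2, over one common observation window and using only the study visits that all states share. The planned Cox model of recovery can carry this.

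Table 1 gives the 12-week maximum to Madhya Pradesh and 16 weeks to Chhattisgarh, while the Sample size section gives the reverse. The two must be reconciled before a common window is set.

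The cost is wording only, and no data are lost. The authors should confirm that the chosen window ends at a visit held in every state.

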The effectiveness of CMAM programme is primarily measured as proportion of children cured or recovered, which is defined as a child achieving WHZ ≥ -2 and/or MUAC ≥125 mm and through other measures like the rate of weight gain, time to recovery, defaulter rate, relapse rate and mortality rate. Sustainability of recovery has long been ignored in the outcomes of SAM treatment as primary focus of treatment was on reducing mortality from SAM. However, in recent years, implementers have begun to consider the extent to which treatment enables a recovery in both short and long terms [12].

SAM is clinically characterized by loss of muscle and fat tissue, reflecting an inadequate intake of energy and protein relative to body requirements. It also has a broader range of pathophysiological changes which are associated with reduced function of the body, specifically metabolic function, oxidative stress, cardiac function, hepatic function, enteropathy, renal and brain function [13]. Nutritional recovery of young children is typically gauged by short-term weight gain. However, an increase in weight does not necessarily reflect an increase in fat-free mass (FFM) as weight gain following severe illness has been shown to be secondary to gains in fat mass (FM) rather than FFM. Despite accounting for height and weight, body mass index (BMI) also does not accurately reflect FFM, as individuals with similar BMI can have significant variations in FFM [14]. Hence, it becomes important to additionally assess body composition (such as FM, FFM and total body water) to evaluate whether these parameters among rehabilitated SAM children are comparable with the normal children however, this has been done in very limited studies. Skinfold thickness and assessment of body composition by bio-electrical impedance analysis (BIA) is a better indicator of energy reserves. Skinfold measurements- tricep and sub-scapular, arm muscle area (AMA) and arm fat area (AFA) provide a simple, easy, and quick yet highly informative assessment of fatness in most patients. The analysis of body composition by BIA method produces estimates of total body water (TBW), fat-free mass (FFM), and fat mass (FM) by measuring the resistance of the body as conductor to a very small alternating electrical current or by administration of radioactive isotope [15, 16]. Application of the combination of these methods may reduce the likelihood of misdiagnosis of high or low lean mass [17].

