### Data collection, cleaning and storage

In the intervention states, the children enrolled in the study will be managed according to the state specific CSAM guidelines and locally produced nutrient dense food supplements. The study will assess the effectiveness of the CSAM programmes in terms of recovery of these children compared to the comparison arm. This will be assessed using anthropometric (length/height and weight) measurements and skinfold thickness (triceps and sub-scapular) to be taken on admission, at sixth week and at discharge by the trained field investigator. For anthropometric measurements, a digital weighing machine with a sensitivity of 10 g to measure weight and a wooden infant-cum-stadiometer to measure length/ height will be used. Length and height will be measured to the nearest 0.1 cm, weight to the nearest 0.01 kg and skinfold thickness to the nearest 0.1 cm. Weighing equipment will be calibrated using standard calibration weights and infant-cum-stadiometer will be calibrated with calibration rods. The skinfold caliper will also be calibrated daily. Before doing the data collection work, all Field Investigators will be trained and also complete anthropometric standardization exercises where their anthropometric measurement skills will be assessed for thoroughness, accuracy and precision. To assess the accuracy and precision of each Field Investigator, their measures will be compared to those of the master trainers, who will be considered the gold standard. Intra-observer technical error of measurement (TEM) and reliability will be calculated using the difference between the two measures of the Field Investigators. Inter-observer TEM and reliability will be calculated by comparing the Field Investigators two measures to the trainer’s measure [27].

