Also, during admission and at discharge, the Field Investigator will administer the questionnaire for capturing child details and incidences of morbidity. Additionally, during admission, data on availability of drinking and sanitation facilities and other household level socio-economic information will be collected. Also,24-h dietary recall, food frequency and food consumption questionnaires will be administered to these children on admission, at sixth week and at discharge to study food consumed by the children, food frequency and compliance of locally produced nutrient dense food supplements provided to the children as part of the intervention. Futhermore, we will also ascertain cause of death of any enrolled child died during the study period.

Besides, first 100 enrolled children in that state who qualifies for body composition measurement i.e. weight on admission > 5 kg, will also be measured for body composition parameters using BIA machine (InBody S10) on admission and at discharge.

Post discharge, the children will be followed up on a monthly basis for anthropometry until 6 months by the field investigators. Additionally, skinfold thickness and body composition assessment of all children will also be repeated at sixth month post discharge. A detailed description of data collection process is shown in Table 2.

**Table 2 Tab2:** Overview of all measurements that will be taken from children

Parameters	Method	Admission/ Baseline	6th Week	12th/16thweek/Exit/Discharge	Post-discharge Follow up^b^
All children enrolled:					
Child details, and history of illness	Questionnaire	**✓**		**✓**	
Drinking water and sanitation facilities and other household socio-economic status		**✓**			
Weight, Recumbent length/ Height,	Digital weighing machine, Infantometer/ Stadiometer	**✓**	**✓**	**✓**	✓
Skinfold Thickness (triceps & subscapular skinfold)	Holtain Skinfold Caliper	**✓**	**✓**	**✓**	✓^c^
Dietary assessment (24-h dietary recall & food frequency) and Consumption of locally produced nutrient dense food	Observation and questionnaire	**✓**^**a**^	**✓**	**✓**	
Body composition; For enrolled sub-sample of children (weight > 5 kg)					
Body fat mass	BIA machine	✓		✓	
Body lean mass					✓^c^

^a^At baseline only the 24-h dietary recall & food frequency assessment will be done

^b^Post discharge, all children will be prospectively followed up for anthropometric measurements on a monthly basis till 6 months by the field investigators

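### Body-composition change is named without scaling to length, so within a state part of any gain in fat-free mass and water is ordinary growth; between states only differential growth remains

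*Protocol article*

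**What the plan says.** Under Secondary research questions, the first question is: "Do state specific CSAM programmes help recovery of a SAM child, as defined by body composition parameters". It is asked for each of the four intervention states.

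For the bio-impedance (BIA) sub-sample, Data analysis states that "change in fat mass, fat free mass and body water will be compared between the four intervention states and the comparison state". The methods it names are "comparison of average change for continuous variable using t-tests" and a linear mixed model, which covers the body-composition parameters among other outcomes, "adjusting for various random and fixed effects across all sites adjusted for differences at baseline". It mentions no length index, length at the second reading or reference values.

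Data collection, cleaning and storage says that the sub-sample "will also be measured for body composition parameters using BIA machine (InBody S10) on admission and at discharge". A further reading is planned six months after discharge. All children have "anthropometric (length/height and weight) measurements and skinfold thickness (triceps and sub-scapular) to be taken on admission, at sixth week and at discharge". Data analysis also says that "average weekly weight gain and height gain will also be compared between the intervention states and the control state".

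Background explains why body composition is worth measuring: "to evaluate whether these parameters among rehabilitated SAM children are comparable with the normal children".

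**The concern.** Fat-free mass and body water rise as a child gets longer, even if the child is no less depleted for its size. The primary outcome avoids this because weight-for-length is already scaled to length. The body-composition outcome, as named, is not. Adjusting for baseline deals with where children start, not with how much they grow between the two readings.

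Two uses of the result are affected.

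- **Within a state.** If a rise in fat-free mass or water is read as recovery, ordinary growth is counted as part of it.
- **Between states.** Growth that is the same in every state cancels against the comparison state. It need not be the same. Children are aged 6 to 59 months. The intervention programmes discharge on reaching the weight-for-length threshold or at a limit of 12 or 16 weeks. The BIA subset is the first 100 children above 5 kg in each state, with no age balance stated for that subset.

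If the second reading is taken at actual exit, a state with more early cures has a shorter interval and less growth. The residual error could then run against a programme as well as for it.

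**Working it through.** **The plan's own figures.** The protocol gives no expected body-composition change to reproduce, only the subset size of 100 per state. Its sample size of 100 per age group concerns cure rate. It reproduces approximately (54.94 × 1.5 = 82.4; 82.4 / 0.80 = 103.0, or 82.4 × 1.20 = 98.9) and has no bearing on this point.

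**Inputs from the protocol.** BIA at admission and discharge; length at the same visits; maximum treatment of 12 or 16 weeks by state; ages 6 to 59 months.

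**Assumptions, not in the documents.** A child of 75 cm and 6.8 kg; fat-free mass 85% of weight; growth g of 0.25 to 1.0 cm per month; 4.345 weeks per month; fat-free mass/length² constant, which means no repletion at all.

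**Step 1: length gain.** ΔL = g × weeks / 4.345.

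**Step 2: proportional rise at a constant index.** f = ((75 + ΔL) / 75)² − 1.

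**Step 3: kilograms.** Starting fat-free mass = 0.85 × 6.8 = 5.78 kg; gain = 5.78 × f.

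| Weeks | g (cm/month) | ΔL (cm) | f | Gain (kg) |
|---|---|---|---|---|
| 12 | 0.25 | 0.69 | 1.8% | 0.107 |
| 12 | 1.0 | 2.76 | 7.5% | 0.434 |
| 16 | 0.25 | 0.92 | 2.5% | 0.143 |
| 16 | 1.0 | 3.68 | 10.1% | 0.582 |

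On the same assumptions the 16-week gain is 0.13 to 0.55 kg for a child of 68 cm and 5.8 kg, and 0.17 to 0.67 kg for one of 90 cm and 9.5 kg.

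**Step 4: what survives between states.** If one state's children exit at 12 weeks and another's at 16, the contrast keeps 0.143 − 0.107 = 0.036 kg at the slow growth rate and 0.582 − 0.434 = 0.148 kg at the fast one, so about 0.04 to 0.15 kg.

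**Step 5: age mix.** Let the 68 cm child growing 1.0 cm per month stand for the younger group (0.55 kg over 16 weeks). Let the 90 cm child growing 0.25 to 0.5 cm per month stand for the older group (0.17 to 0.33 kg). A shift of ten percentage points in age mix between two states then leaves 0.10 × (0.55 − 0.33) = 0.02 kg to 0.10 × (0.55 − 0.17) = 0.04 kg.

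**Treatment limits.** Table 1 gives Madhya Pradesh 12 weeks and Chhattisgarh 16. The Sample size section gives them the other way round. The state to which any interval effect applies is therefore not settled.

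**The case against.** The case against has five parts.

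1. **Silence is not error.** The protocol does not say that change will be analysed in kilograms, and this is a condensed article. The unspecified random and fixed effects could include age or length. This stands in part: a full analysis plan may already deal with the point. But the article does name the endpoint, and what it names is change in the masses and in water, with t-tests on average change and baseline adjustment. None of that is scaled to length.

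2. **Growth can be separated from repletion.** A reader might infer that the two cannot be told apart in this study. The documents do not support that. Length is recorded at the BIA visits, and height gain is compared as an outcome. The gap is in the stated analysis, not in the data.

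3. **The comparator removes much of it.** The rationale frames recovery against the state without the programme, and growth common to all states cancels in that contrast. This stands, and it limits the between-state problem to differential growth. A reader might infer a between-state error of around 0.4 kg by setting a state made up entirely of fast-growing infants against one of older children. The protocol plans equal age groups among the 200 children per state. The BIA subset is not guaranteed to match that balance, but so extreme a contrast is not to be expected.

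4. **Normality is background only.** A reader might infer that the study sets out to show return to normal composition. That sentence is general motivation. The stated aim is impact on anthropometry and body composition, and the analysis plans no such conclusion.

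5. **Adjustment can do harm.** Days between readings are in effect length of stay, which the programme affects because children leave on cure. Conditioning on it can distort the programme effect. Indexing to length also removes any benefit that acts through linear growth. Both stand and shape the remedy.

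**Conclusion.** The point holds in a limited form, for a secondary outcome measured in a sub-sample. As named, the body-composition endpoint is not scaled to length, and baseline adjustment does not supply what is missing.

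For the question asked within each state, the growth component is material: about 0.14 to 0.58 kg, or 2.5% to 10% of fat-free mass, over 16 weeks in the illustrative child. Between states the residual is smaller, about 0.04 to 0.15 kg for a 12- against 16-week exit, and its direction is not fixed.

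All these figures rest on assumed body size, an 85% fat-free share, growth of 0.25 to 1.0 cm per month and a constant index. They illustrate scale and are not estimates for these children. The primary outcome is unaffected.

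**What to change.** In Data analysis:

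- Add change in fat mass/length², fat-free mass/length² and body water/length², using the length taken at the same visit and adjusting for baseline value and age. Name these as the measures that answer the body-composition recovery question.
- Report the kilogram changes alongside and keep height gain as an outcome, so that a benefit acting through linear growth stays visible.
- Leave days between readings out of the main model. Show that adjustment only as a sensitivity analysis.
- Word the conclusion as change in size-adjusted composition relative to the comparison state, not as return to normal, since no reference children are measured.

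Separately, reconcile Table 1 with the Sample size section on which state has the 12-week limit.

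The cost is a few sentences of analysis text. No measurement is added, because length is already collected at these visits.
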